## List of abbreviations

|           |                                                                                                                       |
|-----------|-----------------------------------------------------------------------------------------------------------------------|
| ABC Scale | Activities-specific Balance Confidence Scale                                                                          |
| ADLs      | Activities of daily living                                                                                            |
| BBS       | Berg Balance Scale                                                                                                    |
| BDI-II    | Beck Depression Inventory                                                                                             |
| DSG       | Austrian Data Protection Act                                                                                          |
| GDPR      | General Data Protection Regulation                                                                                    |
| FES-I     | Falls Efficacy Scale                                                                                                  |
| FGA       | Functional Gait Assessment                                                                                            |
| FOGQ      | Freezing of Gait Questionnaire                                                                                        |
| ID        | Identification number                                                                                                 |
| LPLV      | Last Patient Last Visit                                                                                               |
| QL        | Quality of life                                                                                                       |
| LSI       | Last subject in                                                                                                       |
| LSO       | Last subject out                                                                                                      |
| MDC       | Minimum detectable change                                                                                             |
| MMST      | Mini Mental Status Test                                                                                               |
| ND        | Not documented                                                                                                        |
| NW        | Side effect                                                                                                           |
| P         | Break                                                                                                                 |
| PDQ-39    | Parkinson's Disease Questionnaire-39                                                                                  |
| PI        | Post Intervention                                                                                                     |
| R&TTE     | Radio equipment and telecommunications terminal equipment (Radio and Telecommunications Terminal Equipment Directive) |
| Scr       | Screening                                                                                                             |
| SD        | Standard deviation                                                                                                    |
| SNW       | Serious side effect                                                                                                   |
| SUE       | Serious adverse event                                                                                                 |
| THS       | Deep brain stimulation                                                                                                |
| Tir CISA  | Tyrolean Hospitals Act                                                                                                |
| TUG       | Timed-Up-and-Go                                                                                                       |
| TUGman    | Timed-Up-and-Go with manual dual task                                                                                 |
| UE        | Adverse event                                                                                                         |
| UPDRS     | Unified Parkinson's Disease Rating Scale                                                                              |
| 10MWT     | 10-Minute Walk Test                                                                                                   |

# 1. Introduction

## 1.1 Background of the study

Idiopathic Parkinson's syndrome is one of the most common neurological conditions affecting people over the age of sixty, with a prevalence of 6.1 million people worldwide (as of 2016). Since 1990, there has been an increase of 14.5%. ("Global, regional, and national burden of Parkinson's disease, 1990-2016: a systematic analysis for the Global Burden of Disease Study 2016.," 2018).. It is the fastest growing neurological disease in the world (Tönges et al., 2019). In people over 65 years of age, the prevalence is 16,226 cases in Austria and 260,817 cases in Germany (Andlin-Sobocki et al., 2005).. The costs per case amount to 9291 euros in Austria and 11138 euros in Germany (Andlin-Sobocki et al., 2005). (Andlin-Sobocki et al., 2005)..

The cardinal symptoms of idiopathic Parkinson's syndrome are akinesia, rigour, tremor at rest and postural instability in varying degrees. (Keus, S. et al., 2014). Furthermore, oculomotor disorders such as reduced saccadic velocity may occur. (Matsumoto et al., 2011).. Decreased saccade amplitude may be one of the main causes of limitations in the perception of the environment. (Matsumoto et al., 2011).. Changes in saccade parameters in combination with bradykinesia lead to an increased risk of falls in everyday life in those affected (Cucca et al., 2011). (Cucca et al., 2018). This, in turn, can lead to limitations in independence in the activities of daily living (ADLs), which negatively influences the participation of those affected (Keus, S. et al., 2014)..

Alcock and colleagues (2020) show in their study that visual dysfunction correlates with and increases the risk of falls in people with Parkinson's disease. In the treatment of people with Parkinson's disease, visual dysfunction should be appropriately addressed to promote coordination and reduce the risk of falls. (Ambati et al., 2016).

Stuart and colleagues (2018) demonstrated that visual cues improve saccade frequency in people with idiopathic Parkinson's disease. Furthermore, Baker and colleagues (2020) achieved a change in the sequence of first-response body segments when turning during walking through the use of visual cues. As a result, the subjects with idiopathic Parkinson's syndrome regained anticipatory adaptation of eye movements. (Baker et al., 2020).

These findings suggest a positive influence on saccade parameters through targeted eye movement training. Such training potentially also leads to an improved perception of the environment, which could positively influence gait safety and thus reduce the risk of falls.

Neurological physiotherapy for Idiopathic Parkinson's Syndrome at the Reha Zentrum Münster is evidence-based and follows international guidelines for rehabilitation (Keus, S. et al., 2014; Grimes et al., 2019; National Institute for Health and Care Excellence (Great Britain), 2017).. It has not yet been investigated whether additional gaze movement training achieves an additional benefit with regard to the dynamic mobility and fall rate of patients.

## 1.2 Necessity of conducting a study

The current state of research in the field of interventions to improve oculomotor function shows partly controversial results. Matsumoto and colleagues describe a stronger and longer fixation on obstacles in people with idiopathic Parkinson's syndrome compared to healthy people of the same age in the control group. (Matsumoto et al., 2011).. Barbieri and colleagues (2018) describe reduced fixation on an obstacle and prolonged fixation on the ground in individuals with Idiopathic Parkinson's Syndrome. (Barbieri et al., 2018; Reed-Jones & Powell, 2017)(Reed-Jones and Powell, 2017b). In addition, Matsumoto and colleagues find a lower saccade amplitude and a lower number of saccades, indicating a reduced ability to grasp objects and the environment. As a result, the participation of individuals with idiopathic Parkinson's syndrome is reduced due to impaired sensing ability. (Matsumoto et al., 2011)..

Cucca and colleagues (2018) found a correlation of visual ability with the quality of life of the study participants. Thus, improved visual ability could also increase the quality of life of people with idiopathic Parkinson's syndrome. (Cucca et al., 2018).

By 2040, up to 14.2 million people worldwide are predicted to have Idiopathic Parkinson's Syndrome. Due to the increasing prevalence, the need for care in inpatient and outpatient care structures will rise. (Tönges et al., 2019).. Therefore, it seems particularly important that there are interventions for both the inpatient and the outpatient sector to maintain the longest possible independence of those affected. In order to make an intervention as close to everyday life as possible, it must be adapted to the given care structures of the respective setting. In Austria, people with idiopathic Parkinson's syndrome have the option of inpatient rehabilitation every year or every two years. Therefore, it seems reasonable to integrate an intervention in the inpatient rehabilitation setting for 4 weeks and thus test it under "real-life" conditions. (Carpinella et al., 2017; Martinez-Martin et al., 2011; Silva de Lima et al., 2018)..

To develop the intervention for this clinical trial, the *Medical Research Council's* (2006) guidelines for developing complex interventions were used to identify, among other things,

appropriate methods for investigating the research question (identifying the evidence, developing a theory and modelling the process and outcomes). (Craig, P. et al., 2006). Thus, this clinical study can add value to the future care of people with Idiopathic Parkinson's Syndrome. The preservation of independence and the reduction of the need for care of persons with Idiopathic Parkinson's Syndrome should be the overarching goals.

More than one third of falls in people with Idiopathic Parkinson's Syndrome occur as a result of tripping due to impaired vision as a contributing factor (Alcock et al., 2020). This highlights the relevance of fall prevention in maintaining independence in people with Idiopathic Parkinson's Syndrome. The correlation of visual dysfunction and an increased risk of falls suggests that targeted eye and gaze movement training can reduce the rate of falls. (Cucca et al., 2018). Improving the speed of eye and gaze fixation leads to better identification of obstacles, a reduction in gait insecurity and thereby a reduction in the risk of falls (Ambati et al., 2016). In the long term, the independence of people with idiopathic Parkinson's syndrome can be maintained in this way. (Ambati et al., 2016).

### **1.3 Risk-benefit assessment**

The activity-oriented physiotherapeutic programme is basically an evidence-based treatment method based on international guidelines for the rehabilitation of idiopathic Parkinson's syndrome, which is guided by physiotherapists in the course of conventional rehabilitation. This physiotherapeutic measure takes place in both groups to the same extent in addition to the usual inpatient interdisciplinary rehabilitation at the Reha Zentrum Münster. The total amount of training during the rehabilitation stay and its intensity correspond to the cited international guidelines for rehabilitation in idiopathic Parkinson's syndrome. The eye movement training is carried out with the activity-oriented physiotherapeutic programme and is also guided by experienced and trained physiotherapists. Based on clinical experience and literature, it can be assumed that the study participants in the intervention group will benefit at least as much from the treatment as in the standard therapy group.

The intervention is initially carried out in a sitting position in order to achieve habituation to the eye movement training. It is not expected that falls will occur during the intervention as the patients are continuously under physiotherapeutic supervision. Dizziness or eye fatigue could be initially triggered by the training. (Camacho et al., 2019a). This risk is minimised by limiting the duration of treatment to four times 30 minutes per week. Eye movement training will not be performed continuously during the 30-minute period, but intermittently with activity-based training to avoid overload from the outset. The intensity and duration of the interventions are considered low impact. Before, during and after the intervention, any complaints and side

effects are asked about. Since the patients are in the Reha Zentrum Münster for the inpatient rehabilitation stay and the intervention is to be integrated into the daily therapy schedule, there is no additional burden in terms of travel. The expected benefit - the optimisation of treatment and a more efficient rehabilitation - is therefore, according to current medical knowledge, only a low health risk and only a low burden for the patients.

## 2 Study objectives and hypotheses

### 2.1 Purpose of study

The aim of the study is to investigate the effects of an activity-based physiotherapy training programme with eye movement training compared to an activity-based physiotherapy training programme without eye movement training on dynamic balance, mobility, walking speed, health-related quality of life, freezing of gait, fall-associated self-efficacy, depression and fall rate in people with Idiopathic Parkinson's Syndrome. The aim is also to explore the change in eye movements (saccade speed, amplitude, latency, fixation duration) over the intervention period and to evaluate the feasibility of a larger randomised controlled trial using predefined parameters.

### 2.2 Research question

**The research question underlying the study** is as follows:

"Is there a difference between the effects of an everyday physiotherapy exercise programme with versus without gaze movement training on dynamic balance, mobility, walking speed, health-related quality of life, freezing of gait, fall-associated self-efficacy, depression and fall rate in people with Idiopathic Parkinson's Syndrome?"

### 2.3 Study objectives

Thus, four **study objectives** are pursued to deepen the knowledge on effectiveness:

1. Assessment of the effects on dynamic balance (primary endpoint)
2. Investigating the feasibility of a larger randomised controlled trial
3. assessment of the effects on functional mobility with and without manual multi-task, static and dynamic balance, walking speed, health-related quality of life, freezing of gait, fall-associated self-efficacy, depression and fall rate (secondary endpoints).

4. evaluation of the change in eye movements during the intervention, measured once a week in the intervention group over the intervention period.

## 2.4 Null hypotheses

**Primary null hypothesis:** There is no difference between the effects of an everyday physiotherapy training programme with eye movement training and such a training programme without eye movement training on dynamic balance in people with idiopathic Parkinson's syndrome.

**Secondary null hypotheses:** There is no difference between the effects of an everyday physiotherapy training programme with gaze movement training and such a training programme without gaze movement training on functional mobility with and without manual multi-task, static balance, walking speed, health-related quality of life, freezing of gait, fall-associated self-efficacy, depression, fall rate and eye movements during dynamic balance tasks and specific training items in individuals with Idiopathic Parkinson's Syndrome.

## 2.5 Alternative hypotheses

**Primary alternative hypothesis:** There is a difference between the effects of an everyday physiotherapy training programme with eye movement training and such a training programme without eye movement training on dynamic balance in people with idiopathic Parkinson's syndrome.

**Secondary alternative hypotheses:** There is a difference between the effects of an everyday physiotherapy training programme with gaze movement training and such a training programme without gaze movement training on functional mobility with and without manual multi-task, static balance, walking speed, health-related quality of life, freezing of gait, fall-associated self-efficacy, depression, fall rate and eye movements during dynamic balance tasks and specific training items in individuals with Idiopathic Parkinson's Syndrome.

# 3 Study description

## 3.1 Study design

Prospective double-blind randomised controlled pilot study

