#### 4.1.4 Blinding

The raters/test takers of the study will be blinded to the group assignment of the participants, and the participants will be blinded to the study hypotheses.

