### 4.2 Intervention

#### 4.2.1 Treatment scheme

The study includes a screening, a baseline examination, 16 intervention sessions a' 30 min over 4 weeks, a post-intervention testing, a focus group for the participants of the intervention group and a follow-up call 4 weeks after the end of the intervention.

The duration and number of examinations and treatments (Table 1) will take place in the context of the patients' inpatient interdisciplinary rehabilitation. It is ensured that all study participants receive the same number of treatments in total. In addition, all participants must receive 8 30-min sessions of physiotherapy per week, of which 4 are reserved for the study intervention in group 1 or 2 and represent an additional measure. All therapists will be trained on the study interventions and instructions for participants in both groups and will therefore work according to the same principles.

**Table 1:** Treatment regimen of a (screened possible\*) study participant

| Intervention                | Dosage | Time                                                                      | Duration    |
|-----------------------------|--------|---------------------------------------------------------------------------|-------------|
| Screening*                  | 1x     | After verification of suitability by the investigator and patient consent | 10-15 min   |
| Study inclusion             |        |                                                                           |             |
| Baseline investigation      | 1x     | Day 0 after study inclusion                                               | 75-90 min   |
| Intervention groups 1 and 2 | 16x    | Start on day 1 after the baseline examination                             | 30 min each |

|                          |    |                                                                                                                                           |           |
|--------------------------|----|-------------------------------------------------------------------------------------------------------------------------------------------|-----------|
|                          |    | 4 x per week, 4 weeks in total                                                                                                            |           |

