| Postintervention testing | 1x | 4 weeks after the start of the intervention                                                                                               | 75-90 min |
| Focus group              | 1x | 4 weeks after the start of the intervention, only for intervention group 1, at a time interval of >2 hours from post-intervention testing | 45-60 min |
| Follow-up call           | 1x | 4 weeks after end of intervention                                                                                                         | 15 min    |

\*If one or more exclusion criteria are present after screening, the patient will not be included in the study.

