#### 4.2.2 Intervention

The intervention is carried out in addition to the therapy units of the inpatient rehabilitation at the Reha Zentrum Münster. All patient goals not addressed by the study intervention as well as neurotherapeutic therapy measures are thus carried out during the usual therapy units (e.g. auditory cueing, cognitive strategies, endurance training, specific posture training).

*Intervention group (Group 1):* Activity-oriented physiotherapeutic training programme with eye movement training; the training is evidence-based and oriented towards guidelines for rehabilitation in idiopathic Parkinson's syndrome (Keus, S. et al., 2014; Grimes et al., 2019; National Institute for Health and Care Excellence (Great Britain), 2017): for 30 min, 4x per week, for 4 weeks, supervised by the respective physiotherapists.

*Control group (group 2):* Activity-oriented physiotherapeutic training programme i. The standard care is evidence-based and oriented towards guidelines for rehabilitation in idiopathic Parkinson's syndrome (Keus, S. et al., 2014; Grimes et al., 2019; National Institute for Health and Care Excellence (Great Britain), 2017): for 30 min, 4x per week, for 4 weeks, supervised by the respective physiotherapists.

The training therefore includes an individualised training adapted to the Hoehn and Yahr stage, which is overall diverse and variable. The training characteristics listed below apply to the training in both intervention groups. The difference between the two groups is only the eye movement training in combination with the exercises described in more detail below.

- Application of the principles of motor learning (external learning focus, repetition, variability, progression, activity-oriented, goal-oriented)
- Specific functional balance training (static and dynamic balance training, e.g. increasingly moving beyond the body's stability limits, secured by the physiotherapist).
- Transfers such as seat-stand
- Functional exercises to improve joint mobility (e.g. trunk rotation with progressive increase to higher body position).
- Functional strength training
- Coordination training
- Fall prevention training
- Training large movement amplitudes with high intensity

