## **8.2 Possible conflicts of interest**

The investigators' conflicts of interest are enclosed in a separate form. This is a prospective randomised controlled pilot study with physiotherapy intervention and blinded data collection. None of the investigators receives a fee for their work.

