# Instructor Manual for Physiotherapists

## General notes:

- Before the start of the programme, ask about the current health status of the participants.
- The exercises should be performed with the aim of achieving the greatest possible amplitude.
- Participants are allowed to take a break at any time.
- Use physiotherapy equipment as available e. g., chairs, stools, gym mats, gym balls, tennis balls, cones, ropes, step stools, dumbbells, balance boards, coordination hoops, rice, and beans bags.
- Add walking training with different variations (e.g., heel to toe, lateral walking, walking in reverse, crossing obstacles during walking, walking through a slalom course, changing walking directions and speed)
- Add stair climbing training
- The exercises to be carried out are constantly adapted to the participants individually, increasing movement speed as possible, in the course of the 4-week therapy within the given standardised framework.
- The documentation template starts on page 24. As the performing physiotherapist, please document here the exercises performed in the respective weeks with the increase (progression) performed (I-III) and the gaze fixation points performed (A-C).
- If participants feel insecure, they can always hold on to the wall or a chair. Assistance can be given if needed.

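### The protocol calls the trial double-blind, but its own blinding section describes an assessor-blinded trial in which participants and therapists know the treatment

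*Protocol*

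**What the plan says.** The design label appears three times: in the title block, in the synopsis row on study design, and in Section 3.1, each time as "Prospective double-blind randomised controlled pilot study".

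Section 4.1.4 is the only text that says who is blinded to what. On the assessors: "The raters/test takers of the study will be blinded to the group assignment of the participants". On the participants: "the participants will be blinded to the study hypotheses". It does not mention therapists.

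Section 8.2 describes the same trial without the word double-blind, as a "prospective randomised controlled pilot study with physiotherapy intervention and blinded data collection".

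On delivery, Section 4.2.1 states that "All therapists will be trained on the study interventions and instructions for participants in both groups", and Section 4.2.2 states that "The difference between the two groups is only the eye movement training in combination with the exercises described in more detail below".

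Table 1 in Section 4.2.1 schedules a focus group of 45-60 minutes "only for intervention group 1, at a time interval of >2 hours from post-intervention testing". The follow-up call comes 4 weeks after the end of the intervention. Table 2 shows FOGQ, FES-I and falls collected at that call.

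**The concern.** To most readers, double-blind means that participants do not know which treatment they receive. Section 4.1.4 claims something weaker for them: they do not know the hypotheses. A label that promises more than the blinding section delivers will be copied into the registration, which has yet to be made, and into the report.

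What is at stake is how the patient-reported outcomes are interpreted. Blinding the rater protects scores that the rater assigns or times. It does not protect an answer given by a patient who knows which programme he or she is doing. Sections 5.6.1 and 2.4 plan between-group tests on these outcomes, and a reader who trusts the label would discount expectation as an explanation for a difference.

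**Working it through.** No figure of the plan depends on the label, so the check is a comparison of sections and a count of outcomes.

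**Step 1: who is blinded to allocation.**

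| Party | What the protocol provides | Blinded to treatment? |
|---|---|---|
| Raters | Blinded to group assignment (4.1.4, repeated in 4.3.2) | Yes |
| Participants | Blinded to the hypotheses (4.1.4) | No |
| Therapists | No provision; trained in both programmes (4.2.1) | No |

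**Step 2: could treatment be concealed in practice?** By Section 4.2.2 the arms differ only in the eye movement training. Group 1 trains with a poster and wall markers, one-to-one with a physiotherapist. Table 2 places the weekly eye tracking during training in group 1 only. The two Instructor Manuals are separate, and only the one for the intervention group asks the therapist to log gaze fixation points. A therapist trained in both programmes therefore knows the arm, and a participant knows whether gaze exercises are part of the sessions. Knowing the exercises is not the same as knowing which programme is expected to do better, and only the latter is what Section 4.1.4 claims to withhold.

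**Step 3: which outcomes the rater blind protects.** Table 2 lists, besides the screening MMST, 10 secondary clinical outcomes: TUG, TUGman, BBS, FSST, 10MWT, PDQ-39, FOGQ, FES-I, BDI-II and falls.

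- Rater-scored or timed: TUG, TUGman, BBS, FSST, 10MWT = 5.
- Purely patient-reported at post-intervention testing: PDQ-39, FOGQ, FES-I, BDI-II = 4.
- Mixed at post-intervention testing: falls = 1. Section 4.4.13 has falls in the intervention period both observed and asked about.
- Check: 5 + 4 + 1 = 10.
- At the follow-up call: FOGQ, FES-I and falls = 3 of 3 patient-reported. Section 4.4.13 has falls in this period asked about only.

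The primary FGA belongs with the rater-scored outcomes.

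**Step 4: where the focus group falls.** The patient-related timetable in the synopsis, Section 3.5, the opening of Section 4.2.1 and the row order of Table 1 all give the same sequence: post-intervention testing, focus group, follow-up call. Only the interval wording in the focus-group row of Table 1 fails to say before or after. In the listed sequence the session comes after the post-intervention questionnaires and before the 3 follow-up outcomes, and group 2 has no counterpart.

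**The case against.** The strongest defence is that the protocol hides nothing. Section 4.1.4 says exactly who is blinded to what, Section 8.2 claims only blinded data collection, and no sample size, endpoint or test depends on the label. The primary endpoint is scored by blinded raters, both arms receive therapist-led training of equal dose, and Section 5.6.1 already calls the inferential analysis preliminary and a basis for sizing a later trial. No section plans an efficacy claim from self-report alone. All of this stands. It limits the consequence, but it does not make the label correct: the synopsis and Section 3.1 are what many readers will consult.

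Three stronger readings are tempting, and the documents do not support them.

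- *The focus group may come before post-intervention testing and so affect all the self-reports there.* A reader might infer this from the interval wording in Table 1 taken alone. Every listed sequence, including the row order of Table 1 itself, places the session afterwards.
- *The focus group breaks the hypothesis blind.* Its stated purpose is acceptance of the intervention, and its questions are in the case report form, which is not shown. Disclosure of the hypothesis is an inference. Nor does the general requirement in Section 6.3 to inform patients fully show what they are told about the expected result.
- *Falls are simply unblinded self-report.* This is true at follow-up. In the intervention period they are also observed, and the weekly study diaries in both manuals record them.

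**Conclusion.** The label is wrong as written. On the protocol's own description the trial is assessor-blinded, with participants unaware of the hypotheses and with participants and therapists not blinded to treatment. This rests on the text of Section 4.1.4 and on the absence of any other blinding provision, and needs no assumption about behaviour.

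The consequence is confined to secondary outcomes. Between-arm differences in PDQ-39, FOGQ, FES-I and BDI-II, and in falls at follow-up, lack the protection of the rater blind. The documents give no basis for the size or direction of any bias, and none is claimed here. A reader should not infer that the primary FGA scoring is compromised or that the trial is invalid.

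A smaller point concerns the focus group. Because it is held in group 1 only and precedes the follow-up call, it is a limitation of the follow-up FOGQ, FES-I and falls comparisons, whatever is discussed there. Fixing its order relative to post-intervention testing tidies the schedule but does not remove that limitation.

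**What to change.** 1. In the title block, the synopsis and Section 3.1, replace double-blind by *assessor-blinded (participants unaware of the hypotheses; participants and therapists not blinded to treatment)*, and use the same wording in the planned registration.
2. State that between-arm differences in PDQ-39, FOGQ, FES-I and BDI-II, and in falls at follow-up, are not protected by the rater blind and will be reported as such, noting that falls in the intervention period are partly observed.
3. In the focus-group row of Table 1, write *more than 2 hours after* post-intervention testing, in line with the synopsis and Sections 3.5 and 4.2.1.
4. Note the group-1-only focus group as a limitation of the follow-up FOGQ, FES-I and falls comparisons.

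The cost is wording in the protocol and registration and a less favourable design label. No patients, visits or analyses are added.
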